**Outcome measures**

The primary outcome was breast milk volume at 72 hours after delivery. All participants were encouraged to breastfeed their infant within 24 hours of delivery based on Sanpasitthiprasong hospital's standard of care policy of early breastfeeding, frequent breastfeeding, correct positioning and avoiding the use of formula when possible. The breast milk volume was measured with a two-hour interval from last breastfeeding, using an electronic pump (Spectra S2Plus^®^, Spectra Baby USA). The electronic pump was applied for 15 minutes on each breast and the total volume of milk was recorded. Breast milk volume was also measured at 24 hours and 48 hours post-delivery. The breast milk volume at 24 hours post-delivery was used as baseline.

Secondary outcomes were observed during 72 hours after delivery period including:

(1) pregnancy outcomes such as postpartum hemorrhage, endometritis.

(2) neonatal outcomes such as neonatal jaundice, respiratory distress.
(3) adverse effects including headache, dry mouth, diarrhea, muscle cramps, itching, or allergic reactions.

(4) participant satisfaction during the three days’ postpartum period were also recorded.

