**Exclusion criteria**

1. Women who have contraindications for breastfeeding such as human immunodeficiency virus infection
2. Women who have serious peripartum complications leading to inability for breastfeeding such as severe postpartum hemorrhage with hypovolemic shock, cardiac arrest, severe preeclampsia and eclampsia
3. Women with history of domperidone or tea herbal ingredients allergy
4. Women whose neonates are sick and separated from mother

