5. Wang Nam Yen herbal tea will be manufactured by Wang Nam Yen hospital, a community hospital in Sa Kaeo reputed for Thai traditional herbal medicine. Each Wang Nam Yen herbal tea contains sappan (*Caesalpinia sappan* Linn.) 500 mg, licorice (*Glycyrrhiza glabra* Linn.) 500 mg, bale fruit (*Aegle marmelos* L. Corr) 500 mg, ginger (*Zingiber officinale* Roscoe) 500 mg, and jewel vine (*Glycyrrhiza glabra* Linn.) 500 mg. Wang Nam Yen herbal tea will be packed in tea bag (2500 mg) designed for each meal. The herbal tea placebo will be prepared as tea bag for each meal, and the placebo tea bag will be identical with Wang Nam Yen tea bag. Both herbal teas will be prepared by diffusion in 200 mL of warm water for 5 minutes. Interventions will be administered orally three times per day after meals. The first administration will occur 12-18 hours following delivery to ensure sufficient time for the evaluation of any postpartum complications that may have occurred. Domperidone will be administered at 10 mg per dose, as 30 mg of domperidone per day are considered safe and sufficient for increasing breast milk production. Placebo tablets are identical to appearance of domperidone tablet. All participants (T, D, C groups) will be administered 200 mL of tea and a tablet after each meal.

T– The Wang Nam Yen herbal tea treatment group will receive Wang Nam Yen herbal tea and placebo tablet after each meal for three meals per day. This is an intervention arm which is designed to assess the efficacy of Wang Nam Yen herbal tea.

D– The domperidone treatment group will receive herbal tea placebo and a 10 mg domperidone tablet after each meal for three meals per day. This is an active control arm which is designed to be comparator as standard treatment.
C– The placebo control group will receive both herbal tea placebo and a placebo tablet after each meal for three meals per day. This is a placebo control arm which is designed to be a reference group with no treatment.

1. Demographic data will be recorded including age, occupation, monthly income, method of health payment, highest education. Obstetric data will be recorded including gestational age, numbers of pregnancy, numbers of delivery, numbers of antenatal visits for this pregnancy, presence of labor symptoms, indication of cesarean delivery, experience of breast feeding, nurturing environment, baby birthweight, sex of baby, immediate postpartum complication, fluid intake and output, and neonatal complication.

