2. Participants will be asked to collect breast milk after received intervention at 24-72 hours postpartum using automated electric breast pump brand spectra type spectra 2 which has minimal pressure at 10 mmHg and maximum pressure at 300 mmHg. Pump cycle is approximately 42 times per minute. Breast pump will be 2 hours after last breastfeeding and pump for 15 minutes each breast. Breast milk will be recorded as milliliters (ml).
3. Drug adverse events including dry mouth, headache, insomnia, abdominal pain, diarrhea, nausea and urinary retention will be recorded.
4. Fluid intake and output will be recorded. Numbers of breastfeeding per day will be recorded.
5. Changes of bodyweight of mother and neonate will be recorded.
6. Before discharge, participants will be recorded for vital signs, fundal height, lochia color, postpartum complication, neonatal complication and participant satisfaction.
7. Collected data will be analyzed.
8. Result will be reported as standard format.
9. Conclusion, discussion and manuscript preparation.

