**Statistical analysis**

The statistical analysis will be performed on an intention-to-treat basis using Stata/MP software version 15.0 (StataCorp 2017, College Station, TX). Descriptive statistics will be carried out using mean with standard deviation for normal distributed continuous data, and median with interquartile range for non-normal distributed continuous data. Categorical data will be presented as counts and percentage and will be tested for significance with Chi-square test. Continuous data will be assessed for normal distribution using histogram and Shapiro–Wilk test. One-way ANOVA with Bonferroni correction will be used for normal distributed continuous data and Kruskall-Wallis test will be used for non-normal distributed continuous data. Significant level is defined as *p*<0.05.

**Figure 3.** Trial procedure

Placing advertisements in four obstetrics wards

Recruiting participant eligible for inclusion and exclusion criteria

Obtaining informed consent from participants

Randomization into 3 groups

| T (n=40)  Wang Nam Yen herbal tea and placebo tablet | D (n=40)  herbal tea placebo and domperidone tablet | C (n=40)  herbal tea placebo and a placebo tablet |
| --- | --- | --- |

Recording baseline data and first administration of intervention at 12-18 hours postpartum

Recording fluid intake and output, numbers of breastfeeding per day, breast milk volume and
drug adverse events at 24, 48 and 72 hours postpartum

Recording primary and secondary outcomes at 72 hours postpartum

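### The window for maternal and neonatal complications opens at delivery, 12-18 hours before the first dose, so early events that treatment cannot have caused can dilute the arm comparison

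*Protocol*

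**What the plan says.** Under Outcome measures, the protocol sets the period for the secondary outcomes: "Secondary outcomes were observed during 72 hours after delivery period including". The first two groups listed are "1) pregnancy outcomes such as postpartum hemorrhage, endometritis" and "2) neonatal outcomes such as neonatal jaundice, respiratory distress".

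Trial procedure places the start of treatment later and gives the reason: "The first administration will occur 12-18 hours following delivery to ensure sufficient time for the evaluation of any postpartum complications that may have occurred". Figure 3, in the Statistical analysis section, repeats the timing: "Recording baseline data and first administration of intervention at 12-18 hours postpartum".

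Complications are recorded at two points. The obstetric data in Trial procedure include "immediate postpartum complication, fluid intake and output, and neonatal complication". The list of items taken before discharge includes "postpartum complication, neonatal complication and participant satisfaction". The protocol mentions no onset time and no rule linking the two records.

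Two exclusion criteria bear on early events. One removes "Women who have serious peripartum complications leading to inability for breastfeeding such as severe postpartum hemorrhage with hypovolemic shock" and comparable conditions. The other removes women whose newborns are ill and kept apart from them.

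Statistical analysis applies a Chi-square test to categorical data on an intention-to-treat basis. It does not restrict the test to events after dosing.

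**The concern.** The stated outcome period starts at delivery and treatment starts 12-18 hours later. The protocol itself expects that complications may occur in between, since that is its reason for the delay. Taken as written, an event in those hours falls inside the outcome period of whichever arm the woman is in.

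Such an event carries no information about the tea or domperidone. It adds roughly the same number of events to every arm and pulls a risk ratio towards 1. For a safety comparison that is the unhelpful direction, because a real increase in complications looks smaller. With 40 women per arm there is already little information on uncommon events.

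The early and the pre-discharge records could also both hold the same event, once as a baseline feature and once as an outcome. The label for neonatal complications is the same in both lists.

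**Working it through.** **Inputs from the protocol**

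- Outcome period: 0 to 72 hours after delivery (Outcome measures).
- First dose: 12 to 18 hours after delivery (Trial procedure; Figure 3).
- Planned size: 40 women per arm (Sample size calculation).
- Timing of complications within the 72 hours: not given.

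**The plan's own figure.** The protocol gives no figure for the complications. Its only sample-size figure concerns milk volume, and it reproduces: 3 × (1.65 + 0.84)² × 136.1² / (191.3 − 91.4)² = 34.52 per group. No complication rate enters it, so a change of the complication window leaves it as it is.

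**Share of the window before dosing**

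- First dose at 12 hours: 12/72 = 16.7%, leaving 72 − 12 = 60 hours.
- First dose at 18 hours: 18/72 = 25.0%, leaving 72 − 18 = 54 hours.

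**Dilution.** Let f be the share of control-arm events that occur before the first dose, and RR the true risk ratio for later events. Assume that the pre-dose risk is the same in each arm and that events are uncommon enough for early and late risks to add. The risk ratio over the full 72 hours is then

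observed RR = f + (1 − f) × RR.

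| f | Basis | True RR 2.0 appears as | True RR 0.5 appears as |
|---|---|---|---|
| 16.7% | even spread, dose at 12 h | 0.167 + 0.833 × 2.0 = 1.83 | 0.167 + 0.833 × 0.5 = 0.58 |
| 25.0% | even spread, dose at 18 h | 0.25 + 0.75 × 2.0 = 1.75 | 0.25 + 0.75 × 0.5 = 0.63 |
| 50% | assumed | 0.50 + 0.50 × 2.0 = 1.50 | 0.50 + 0.50 × 0.5 = 0.75 |
| 80% | assumed | 0.80 + 0.20 × 2.0 = 1.20 | 0.80 + 0.20 × 0.5 = 0.90 |

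Only the first two values of f come from the protocol's own times, and they still need the assumption of an even spread. The last two show how the result moves if events cluster early, and the protocol offers no support for any particular value.

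**Which events are left.** The exclusions remove haemorrhage grave enough to prevent breastfeeding and newborns ill enough to be separated. A milder haemorrhage, or distress in a baby who stays with the mother, remains eligible and lies within the stated period.

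**The case against.** The strongest reply is that the sentence under Outcome measures describes a period of observation and gives no counting rule. Which recorded events enter the comparison could be settled in an analysis plan that is not shown. Early complications have their own record, separate from the one before discharge, so the two could be told apart at analysis. A reader might infer that the protocol definitely counts pre-dose events as treatment outcomes, or counts them twice. It says neither. What stands is that the only period it states is anchored to delivery and nothing in it narrows that. Separation by two records is partial unless onset time is collected, and an analysis plan cannot supply a time that was never recorded.

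A reader might also infer a biased comparison, or a chance imbalance in early events that passes too often for a drug effect. The protocol does not support this. Allocation is by sealed opaque envelope with participants and investigators blinded, so events unrelated to treatment should balance on average. The Chi-square test already allows for chance imbalance at its nominal level.

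It is tempting as well to take the 1.50 or 1.20 in the table as the size of the problem, or to extend it to all four named complications. Those values rest on assumed shares, and nothing in the protocol shows endometritis or jaundice arising before 12-18 hours.

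Finally, under intention to treat, counting from randomisation is a recognised alternative to counting from first dose. That is a fair point. However, the protocol gives no clock time for randomisation; Figure 3 only places it before the first dose. Counting from first administration is compatible with intention to treat if every randomised woman stays in her assigned arm.

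**Conclusion.** The point holds as a loss of sensitivity in the secondary comparison of maternal and neonatal complications. The stated window includes 12-18 hours in which treatment can have had no effect, and some eligible events can fall there. With an even spread of events, a true risk ratio of 2.0 would appear as 1.83-1.75 and one of 0.5 as 0.58-0.63. The dilution would be greater only if a larger share of events came early, which the protocol neither states nor excludes. It may well differ between the complications.

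The conclusion rests on the outcome period being applied as written and on equal pre-dose risk across arms. It does not touch milk volume at 72 hours or the sample size. The correction is worthwhile because it is cheap and bears on the safety comparison, but it does not threaten the trial's main result.

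**What to change.** Amend Outcome measures so that the maternal and neonatal complications compared between arms are those with onset from first administration to 72 hours after delivery. Keep all randomised women in their assigned arms, and say which start time applies to a woman who takes no dose. Record the onset time of each complication. Tabulate events already present at first dose as baseline characteristics, using the early complication record that Trial procedure already provides for. Report the full 72-hour count alongside, so that no information is lost.

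The cost is one or two sentences, one extra field on the case record form and slightly fewer events in the main comparison. No dose, visit or sample size changes.

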**Trial procedure**

1. Literature review for relevant studies.
2. Drafting trial protocol and design case record form for ethical committee approval.
3. Plan for education for standard postpartum care and breastfeeding to women aged

15 to 41 years who deliver via cesarean section at 28 to 42 weeks’ gestational age at Sunpasithiprasong Hospital, Ubon Ratchathani, Thailand during February 2017 to

September 2017 and provide written informed consent.

1. Recruiting participants according to inclusion and exclusion criteria by placing advertisements in four obstetrics wards.
2. Giving trial information to potential participants using obstetrician and nurse in each obstetric ward and participant information sheet to confirm participant understanding of trial objective, procedure, benefits, and risks. If potential participants are willing to participate in trial, they will be asked to sign informed consent form with understanding that they can quit from trial at any time without any consequence.
3. Participants will be randomly assigned into three groups based on numbers generated by a table of random numbers in blocks of three: 1) Wang Nam Yen herbal tea and placebo tablet (T group), 2) domperidone tablet and placebo herbal tea (D group), 3) placebo tablet and placebo herbal tea (C group).
4. All study interventions will be prepacked and sealed in opaque packages, for three consecutive days of postpartum use. Participants and investigators were blinded to the treatment assignment. Randomization ID will be TD001 to TD120.

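### Adverse-event recording ends 72 h after delivery, but the plan does not say when the three-day treatment course ends; a full nine-dose course would usually finish after that cut-off

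*Protocol*

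**What the plan says.** Three parts of the protocol bear on this.

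- **Safety window.** Outcome measures states: "Secondary outcomes were observed during 72 hours after delivery period including" maternal and neonatal outcomes, adverse effects and satisfaction. Figure 3 (under Statistical analysis) schedules "drug adverse events at 24, 48 and 72 hours postpartum" and closes with "Recording primary and secondary outcomes at 72 hours postpartum". Both count from delivery.
- **Treatment course.** Trial procedure says the interventions are "sealed in opaque packages, for three consecutive days of postpartum use". It also says "Interventions will be administered orally three times per day after meals", and "The first administration will occur 12-18 hours following delivery". No section gives a total number of doses or a time for the last one.
- **Discharge record.** Trial procedure adds: "Before discharge, participants will be recorded for vital signs, fundal height, lochia color, postpartum complication, neonatal complication and participant satisfaction". This carries no 72 h limit, but the drug adverse events are a separate item and are not in it. That separate item gives no time limit of its own. The time of discharge is not stated, and no contact after discharge is described.

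**The concern.** The recording window starts at delivery and lasts 72 h. The treatment period starts 12-18 h later and is described as three days. Unless the course is meant to be cut off at the 72 h assessment, the two cannot end together.

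What is at stake is the coverage of the harm data. Outcome measures names itching, allergic reactions and diarrhea as outcomes, and any of these could follow the final doses. If those doses are taken after the last recording, the adverse-event rates describe only part of the regimen supplied. A statement that the tea or domperidone was well tolerated would then reach further than the data. An analysis plan cannot repair this later, because data that were not collected cannot be analysed. The 72 h milk-volume endpoint is not affected.

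**Working it through.** The protocol gives no figure for the time of the last dose, so there is none to reproduce.

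**Inputs from the protocol:** first dose at 12-18 h (Trial procedure); three doses a day, after meals (Trial procedure); three days of supply (Trial procedure); last adverse-event recording at 72 h (Outcome measures, Figure 3).

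**Assumptions:** the meal timetables below, births spread evenly over 24 h, and the first dose taken at the first meal inside the 12-18 h window. Birth times with no meal in that window are left out.

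**Reading A: three full days, 3 × 3 = 9 doses.**

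*Even 8 h spacing.* Last dose = start + 8 × 8 h = start + 64 h. Start 12 h gives 76 h and start 18 h gives 82 h. That is 4-10 h past the cut-off for every permitted start.

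*After meals at 07:00, 12:00 and 17:00.* The ninth dose is eight meals after the first.

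| First dose at | Compliant birth times | First dose, h after delivery | First to ninth dose | Ninth dose, h after delivery | Doses after 72 h |
|---|---|---|---|---|---|
| 07:00 | 6 h | 12-18 | 58 h | 70-76 | 0 if started before 14 h (2 h of birth times), otherwise 1 (4 h) |
| 12:00 | 5 h | 12-17 | 67 h | 79-84 | 1 (eighth dose at 65-70) |
| 17:00 | 5 h | 12-17 | 67 h | 79-84 | 2 (eighth dose at 74-79) |

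Compliant birth times total 6 + 5 + 5 = 16 h of the 24. For the other 8 h (33%) no meal falls in the window.

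- Ninth dose after 72 h: (16 − 2)/16 = 87.5%.
- No dose outside: 2/16 = 12.5%. One dose outside: (4 + 5)/16 = 56%. Two doses outside: 5/16 = 31%. Three doses outside: none.

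*Other timetables.*

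- Meals at 08:00, 12:00 and 18:00 again give 87.5%.
- Meals at 07:00, 11:30 and 16:30 give the lowest share. There are 6 + 4.5 + 5 = 15.5 h of compliant birth times. A breakfast start puts the ninth dose 57.5 h later, so starts before 14.5 h finish in time: (15.5 − 2.5)/15.5 = 84%.
- Meals at 08:00, 13:00 and 20:00 give the highest share. A breakfast start puts the ninth dose 60 h later, at 72-78 h, so essentially 100% overrun.

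**Reading B: three calendar days from the day of the first dose, ending with the third evening meal.** With meals at 07:00, 12:00 and 17:00, a breakfast start ends at 70-76 h, a lunch start (+53 h) at 65-70 h, and an evening start (+48 h) at 60-65 h. Only breakfast starts after 14 h overrun: 4/16 = 25%. With meals at 07:00, 11:30 and 16:30 the share is 3.5/15.5 = 23%. With meals at 08:00, 13:00 and 20:00 (6 + 5 + 6 = 17 h compliant) it is 6/17 = 35%.

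**Reading C: dosing stops at 72 h after delivery.** No dose falls outside the window. With meals at 07:00, 12:00 and 17:00, women would then have had seven doses (31%), eight (56%) or nine (12.5%), depending on birth time. The time observed after the last dose is only what remains before the 72 h recording. That is at most one gap between meals, 14 h overnight in this timetable.

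**The case against.** The strongest reply is that the protocol never mentions nine doses. The supply is described in terms of postpartum days, and the satisfaction item in Outcome measures calls the observation period the three days after birth. Reading C is therefore natural, and under it every dose is inside the recording window. This stands: the nine-dose course is an inference, and an overrun for most women is conditional on it. What remains is that the protocol does not say which reading applies, and that under Reading C nothing is scheduled beyond 72 h.

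A second reply is that the safety record does not simply stop. This also stands in part. Maternal and neonatal complications are recorded before discharge with no 72 h limit. A reader might infer that everything after the last doses goes unobserved, or that the newborn has no later record; the discharge item contradicts both. It does not cover the listed drug adverse events, and since the time of discharge is not given, how much it adds cannot be settled from the document.

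A third reply is that all three arms share the same window, and a rate labelled as covering 72 h after delivery is correctly labelled. That is right. A reader might infer that the trial will understate the harm of the tea and of domperidone, or that the comparison between arms is biased. The document gives no figure on reactions after the final doses, so neither is shown.

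Finally, a reader might infer that up to three doses are missed. That requires first doses later than 18 h, which the protocol's own start window excludes.

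**Conclusion.** The concern holds as an unresolved mismatch between two clocks in the protocol, with limited consequences. Adverse-event recording ends 72 h after delivery, while the end of treatment is not defined.

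- If nine doses are meant, the ninth falls at 76-82 h (even spacing) or about 70-84 h (after meals). It is later than 72 h for about 84-100% of compliant birth times, typically leaving one or two doses outside recording.
- If calendar days are meant, the share falls to roughly a quarter to a third of compliant birth times.
- If dosing stops at 72 h, no dose is missed, but no adverse-event recording follows the 72 h assessment.

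The after-meal percentages rest on assumed meal times, births uniform over the day, and first doses inside 12-18 h. The even-spacing result needs only the start window and nine doses. The supported conclusion is that reported adverse-event rates may not cover the whole regimen supplied. The document does not support a claim of bias between arms or of demonstrated under-reporting of harm.

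**What to change.** 1. Reconcile Outcome measures, Trial procedure (packaging, first administration, adverse-event and discharge items) and Figure 3, so that the number of doses, the time of the last dose and its relation to the 72 h assessment are explicit. Which dosing rule applies is for the investigators to state.
2. Define the adverse-event window by treatment: from first dose to a stated interval after each woman's actual last dose. Record the time of that dose.
3. Add the drug adverse-event questions to the existing pre-discharge record. If a woman can leave before her last dose or before the window closes, a telephone call would be needed.
4. Leave the 72 h milk-volume endpoint as it is.

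The cost is protocol wording, a slightly longer discharge form and possibly some calls. Adverse-event counts may come out slightly higher. No extra participants or clinical procedures are needed.
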